# Effect of ketamine combined with magnesium sulfate in neuropathic pain patients (KETAPAIN): study protocol for a randomized controlled trial

**DOI:** 10.1186/s13063-017-2254-3

**Published:** 2017-11-03

**Keywords:** Ketamine, Neuropathic pain, Magnesium sulfate, *N*-methyl-d-aspartate receptor, Placebo

## Abstract

**Background:**

Neuropathic pain is difficult to treat, and the efficacy of recommended drugs remains limited. *N*-methyl-d-aspartate receptors are implicated, and antagonists are a pharmacological option. Ketamine is widely used in French pain clinics, but without consensus or recommendations. Furthermore, the association of ketamine with magnesium has been poorly studied. The aim of the present study is to evaluate the benefit of ketamine with or without magnesium in refractory neuropathic pain.

**Methods/design:**

A randomized, double-blind, crossover, placebo-controlled study will be performed in Clermont-Ferrand University Hospital, Clermont-Ferrand, France. The aim is to evaluate the effect of ketamine with or without magnesium in 22 patients with neuropathic pain. Intravenous ketamine/placebo, ketamine/magnesium sulfate, or placebo/placebo will be administered consecutively to each patient, in random order, once at 5-week intervals. The primary endpoint is the AUC of pain intensity assessed on a 0–10 Numeric Pain Rating Scale for a 5-week period. Data analysis will be performed on an intention-to-treat basis, and all statistical tests (except primary analysis) will be performed with an α risk of 5% (two-sided).

**Discussion:**

Considering the poor efficacy of the drugs available for neuropathic pain, ketamine with or without magnesium sulfate may be a valuable therapeutic option that needs to be standardized.

**Trial registration:**

EudraCT number–2015-000142-29. Registered on April 9, 2015; version 1.4

**Electronic supplementary material:**

The online version of this article (doi:10.1186/s13063-017-2254-3) contains supplementary material, which is available to authorized users.

## Background

Neuropathic pain (NP), whatever the etiology or topography, presents with a number of clinical characteristics: sensory deficit, hypoesthesia, electric shock-like pain, allodynia, or hyperalgesia [1]. *N*-methyl-d-aspartate receptors (NMDARs) are involved in the development of NP and may provide an avenue to a pharmacological tool for treatment. Ketamine, an NMDAR antagonist, has been used for a number of years for the treatment of NP. In animals, it decreases NP symptoms [2–10]. In humans, ketamine at infra-anesthetic doses has shown some efficacy in postoperative pain [11], refractory pain [12], phantom limb pain [13], postherpetic neuralgia [14], and complex regional pain syndrome (CRPS) [15–17]. Most clinical studies showing efficacy were retrospective [18–21], open prospective [22, 23], or clinical reports [24, 25]. However, a few randomized, placebo-controlled, double-blind studies have also been published [15–17]. Ketamine appears to be well tolerated at low doses, with little psychodysleptic effect [16, 19, 20, 22, 23].

Another NMDAR modulator, magnesium sulfate, is a physiological blocker of NMDAR and has also been shown to be effective in the treatment of NP. In animal NP models, it decreased cold allodynia and thermal and mechanical hyperalgesia [26–29] and increased the analgesic effect of morphine [27, 30]. In humans, it is well tolerated and has shown efficacy against NP in patients with cancer [31], headache [32], and postoperative pain [33], as well as in the frequency of pain paroxysms and in the emotional component [34].

Concerning the ketamine-magnesium sulfate interaction, a preclinical study showed a synergistic effect, blocking the hyperthermia caused by systemic administration of morphine [35]. A recent randomized, prospective, double-blind study [36] of patients undergoing scoliosis surgery showed that magnesium sulfate combined with ketamine had a greater beneficial effect on postoperative pain and morphine consumption than ketamine alone. Furthermore, patients receiving ketamine combined with magnesium sulfate reported better sleep. Magnesium sulfate and ketamine act on different sites of the NMDAR channel, and this could explain their synergistic role. This combination is hypothesized to reduce ketamine dosage and diminish its adverse events, although another randomized, double-blind, controlled trial [37] showed no significant difference in the occurrence of adverse events among patients receiving ketamine either alone or combined with magnesium sulfate. Given the lack of randomized clinical trials of ketamine or the combination of ketamine and magnesium, the objective of the present randomized, controlled, double-blind trial is to assess the efficacy of intravenous ketamine with or without magnesium in patients with NP.

## Methods/design

This is a randomized, placebo-controlled, double-blind, crossover, single-center clinical study with intravenous ketamine/placebo, ketamine/magnesium sulfate, and placebo/placebo injections given to each patient. This clinical trial is reported according to the Standard Protocol Items: Recommendations for Interventional Trials (SPIRIT) guidelines (*see* Additional file 1) and performed in Clermont-Ferrand University Hospital, Clermont-Ferrand, France. Patients meeting the inclusion criteria will sign a consent form after receiving oral and written information from a physician investigator involved in this project. During this consultation, they will fill out a Numeric Pain Rating Scale (NPRS), as well as the Diagnosing Neuropathic Pain 4 Questions [38] in order to detect NP, and they will be asked to keep a daily pain diary (mean daily pain and maximum pain on NPRS, and concomitant analgesic treatment) for 14 days before the first course of treatment. After inclusion, patients will be randomly assigned to ketamine-placebo, ketamine-magnesium sulfate, or placebo-placebo for 1 month, in random order, with a washout period of 5 weeks between every treatment (Fig. 1). At each injection, the patients will undergo a number of tests for assessment of (1) pain (NPRS, Brief Pain Inventory [BPI] [39], McGill Pain Questionnaire [40], and Patient Global Impression of Change [PGIC] [41]), (2) NP (Neuropathic Pain Symptom Inventory [NPSI] [42]), (3) anxiety and depression (Hospital Anxiety and Depression Scale [HADS] [43], (4) quality of life (36-item Short Form Health Survey [SF-36] [44]), and (5) quality of sleep (Pittsburgh Sleep Quality Index [PSQI] [45]). All questionnaires will be administered before each ketamine injection in order not to influence the results because of the possible ketamine adverse events. To check for any adverse events, subjects will be called by phone on the day following each injection.

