#### Secondary outcome measure

Secondary endpoints are the evaluation of pain (NPRS, NPSI, BPI, McGill Pain Questionnaire, PGIC), anxiety and depression (HADS), quality of life (SF-36), and quality of sleep (PSQI) using a variety of scales and questionnaires. Furthermore, the intensity of the average and maximum pain scores as well as concomitant analgesic treatments will be reported in a daily pain diary. The various assessments and questionnaires are summarized in Fig. 2.

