### Allocation concealment

On the day of the first visit, inclusion and exclusion criteria are verified, and written informed consent is obtained by the physician. A clinical nurse independent from the protocol obtains the randomization number from the hospital pharmacy, and the patient is then randomized into one of the three groups. The assignment to the treatments will follow a predetermined randomization list and is generated using random blocks by a clinical research associate totally independent from the protocol. The randomization list and a copy will be edited, placed in a sealed envelope, and handed over to the Clermont-Ferrand University Hospital Pharmacy and to the coordinating center, the Clinical Research Center of Clermont-Ferrand University Hospital.

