### Sample size calculation

To highlight the analgesic efficacy of intravenous ketamine in patients with intractable NP, sample size estimation was based on a pilot study done at the pain clinic of the University Hospital of Clermont-Ferrand (administration of intravenous ketamine in a similar open-label population), showing an AUC (28 days) of the intensity of pain of 164 ± 38 (unpublished data). Furthermore, in a study comparing similar treatments (ketamine and placebo) in a different chronic pain setting (CRPS), the AUC graph estimate suggested a 35% reduction in AUC (at 28 days), that 18 patients are needed to detect a minimum difference of 57 in the primary outcome, with a two-sided type I error of 1.67% (to take account of multiple comparisons), statistical power of 90%, and an intraindividual correlation coefficient of 0.5 (owing to the crossover design and no carryover effect assumed) [46]. Considering data from our center, a recent study [46] (NCT01602185) currently submitted to a peer-reviewed journal but not yet published clearly shows that pain evaluation remains the same from 28 days to 60 days. Ultimately, allowing for patient dropout for adverse events or premature withdrawal, we plan to recruit 22 subjects.

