### Statistical analysis

Statistical analysis will be performed on an intention-to-treat basis using Stata software (version 13; StataCorp, College Station, TX, USA) for a two-sided type I error at α = 5%. Continuous data will be described as mean ± SD or median (IQR) according to the statistical distribution (assumption of normality studied by Shapiro-Wilk test). Categorical parameters will be described as number and percent. The primary endpoint (AUC of pain intensity based on NPRS) will be compared between groups by repeated measures analysis of variance (ANOVA) for crossover designs, taking account of the following effects: treatment group (ketamine versus placebo), sequence, subject (as random effect), and carryover. Then, the “sequence × treatment” interaction will be tested; if it is significant, statistical analysis will cover only the first period of the crossover study. The normality of residuals will be studied. When quantitative endpoints do not meet the normality assumption, a nonparametric paired Wilcoxon test will be used. Sensitivity analysis will determine the statistical nature of missing data to apply the most appropriate imputation approach.

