Statistical analyses of secondary outcomes (NPSI, BPI, HAD, SF-36, PSQI and McGill Pain Questionnaire scores) will be performed similarly to those for the primary endpoint. For categorical parameters (PGIC, analgesic response), the Stuart-Maxwell test for proportion paired data or a generalized linear mixed model will be used, taking the above effects into account. Random-effects models, useful to model between- and within-subject variability, will be performed for the effects described for the crossover ANOVA, to compare the additive analgesic efficacy of associating magnesium sulfate versus placebo to ketamine, and to study the evolution of pain and analgesia with the waning of the intravenous administration. In case of omnibus *p* value < 0.05, a post hoc analysis for multiple comparisons (inflation of type I error) will be applied using the Tukey-Kramer test. For non-crossover comparisons, the usual statistical tests will be performed: (1) for quantitative parameters, ANOVA or Kruskal-Wallis test if the conditions for parametric tests are not met (normality and homoscedasticity on Fisher-Snedecor test); and (2) for categorical variables, the chi-square test or Fisher’s exact test. When appropriate (*p* < 0.05), an appropriate post hoc test will be applied: Tukey-Kramer post hoc ANOVA or Dunn post hoc Kruskal-Wallis. As discussed by Feise [47], type I error (α) will not be adjusted systematically, but rather on a case-by-case basis, in the light of clinical rather than exclusively statistical considerations.

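### The 14-day run-in pain diary has no stated role in the primary analysis, which matters if the analysis falls back to period 1 with about 6 to 7 patients per arm

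*Protocol article*

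**What the plan says.** Under Methods/design, patients record mean and maximum daily pain on the NPRS, and their analgesics, "for 14 days before the first course of treatment". The primary outcome is the AUC of the same scale over 35 days from treatment.

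Under Statistical analysis, the primary model contains "treatment group (ketamine versus placebo), sequence, subject (as random effect), and carryover". No baseline or run-in term is listed. A sequence-by-treatment interaction is then tested, and "if it is significant, statistical analysis will cover only the first period of the crossover study". The same section covers non-crossover comparisons with a general rule: "for quantitative parameters, ANOVA or Kruskal-Wallis test if the conditions for parametric tests are not met". It names no covariate there.

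Under Secondary outcome measure, "the intensity of the average and maximum pain scores as well as concomitant analgesic treatments will be reported in a daily pain diary". The diary as a whole therefore has a use; its 14 run-in days have no separate one.

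Two alpha levels appear. The sample size is computed "with a two-sided type I error of 1.67% (to take account of multiple comparisons"), and the analysis section opens "for a two-sided type I error at α = 5"%.

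**The concern.** In the crossover analysis each patient is their own control, and the patient effect removes stable differences in pain level. One pre-treatment measurement adds little to that.

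Restricting the analysis to period 1 takes this protection away. Each patient then contributes one AUC, so the patient, sequence and carryover terms cannot be estimated separately and only treatment is left. All between-patient variation in pain goes into the error term, and chance baseline differences between arms of six or seven patients go uncorrected. The run-in diary uses the same scale, is recorded just before period 1 and is already collected, which makes it the obvious covariate. If the rule fires and no covariate has been fixed, the primary result rests on a small unadjusted comparison, or on an adjustment chosen after the data are seen.

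**Working it through.** **Inputs.** From Sample size calculation: SD 38, difference 57, two-sided alpha 1.67%, power 90%, within-patient correlation 0.5, 18 evaluable patients, 22 recruited. From Statistical analysis: alpha 5%. Assumed: equal allocation over three arms in period 1, and a correlation r between mean run-in NPRS and the period-1 AUC. The protocol's 0.5 is between a patient's repeated outcomes, so it is not r.

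**The protocol's own figure.** For a paired comparison, SD of the difference = 38 × √(2 × (1 − 0.5)) = 38, and n = (2.393 + 1.282)² × 38² / 57² = 6.0. That is 7 rounded up, or 10 with the t distribution. The stated 18 is not reproduced; with 18 the paired comparison has over 99.9% power on these inputs. This is a separate matter. Here it shows only that the crossover has ample power on the stated inputs, so any shortfall lies in the fallback.

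**Group size.** 18/3 = 6 and 22/3 = 7.3 per arm. Under Missing data, patients who miss a treatment block are excluded, so the lower figure is realistic.

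**Unadjusted fallback.** SE = 38 × √(2/n): 21.9 for n = 6 and 20.3 for n = 7. The noncentrality 57/SE is 2.60 and 2.81. Power comes from the noncentral t with 3n − 3 = 15 or 18 degrees of freedom. The 95% CI half-width is 2.131 × 21.94 = 46.8 or 2.101 × 20.31 = 42.7, against a target difference of 57.

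**Adjusted fallback.** ANCOVA multiplies the variance by (1 − r²) × (1 + 1/(df − 1)), with df = 3n − 4 = 14 or 17. For n = 6 and r = 0.5 this is 0.75 × (1 + 1/13) = 0.808, so SE = 21.94 × √0.808 = 19.7. A simulation of 20,000 runs per setting gave 0.81 (n = 6) and 0.80 (n = 7) at r = 0.5, in agreement.

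Power for a difference of 57:

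| Analysis | Variance ratio (n = 6; 7) | Alpha 1.67% (n = 6; 7) | Alpha 5% (n = 6; 7) |
|---|---|---|---|
| Unadjusted | 1 | 48%; 58% | 68%; 76% |
| ANCOVA, r = 0 | 1.08; 1.06 | 44%; 54% | 64%; 73% |
| ANCOVA, r = 0.3 | 0.98; 0.97 | 49%; 59% | 69%; 77% |
| ANCOVA, r = 0.5 | 0.81; 0.80 | 58%; 69% | 77%; 84% |
| ANCOVA, r = 0.7 | 0.55; 0.54 | 77%; 86% | 90%; 95% |

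**Break-even.** The 95% CI narrows only if r exceeds about 0.29 (n = 6) or 0.26 (n = 7). At r = 0.5 its half-width is 42.3 or 38.3.

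**28 or 35 days.** The SD and difference are 28-day values. Scaled by 35/28 they become 47.5 and 71.25. Their ratio stays 1.5, so the power figures do not change.

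**The case against.** The strongest objection is that this rests on silence in a condensed article. The protocol says the analysis covers only period 1; it does not say that analysis is unadjusted, and a full protocol or SAP could name the covariate. The sentence on ANOVA and Kruskal-Wallis never mentions the first-period rule, so applying it there is an inference. That stands as a limit on the wording. Even so, the article fixes the model effects, the trigger, the retained data and the tests for non-crossover comparisons, and the natural reading of these together is an unadjusted comparison.

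Four stronger readings are tempting and should be resisted:

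- A reader might infer that the diary is unused. It is a listed secondary measure; only the run-in days lack a stated analytic role.
- A reader might infer that adjustment is free. Data collection is, but the analysis spends a degree of freedom and estimates a slope from 18 to 21 patients, so it loses precision below r of about 0.3.
- A reader might infer that adjustment recovers most of the lost power. That needs r of 0.7 or more, which the documents do not support. At 0.5 the fallback misses 90% at either alpha.
- A reader might take 43% (alpha 1.67%) or 65% (alpha 5%) as the unadjusted power at 6 per arm. Those figures use the variance of two arms only; the ANOVA would pool three.

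It is also fair that the expected gain is small. If no interaction exists and it is tested at 5%, the rule fires in about one trial in twenty. At r = 0.5 and 6 per arm, the 10-point gain at alpha 1.67% is then worth about 0.05 × 10 = 0.5 points overall. And if the first-period rule were dropped, most of this point would go with it.

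**Conclusion.** The point holds as a minor improvement to the stated method. No error of fact is involved, and the main crossover analysis is hardly affected. If the interaction rule reduces the analysis to period 1, the plan as most naturally read gives an unadjusted comparison with roughly half to three quarters power, depending on alpha and on 6 or 7 patients per arm. Prespecified adjustment for run-in pain would add about 8 to 11 points at r = 0.5 and about 19 to 29 points at r = 0.7. It would add almost nothing at 0.3 and cost about 3 to 4 points at 0.

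This rests on equal allocation, on the protocol's SD and difference, on a variance common to the three arms, and on a correlation that the documents do not give.

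**What to change.** Add one sentence to Statistical analysis: any first-period-only analysis, whether kept as the fallback or as a sensitivity analysis, will be an ANCOVA of the 35-day AUC on treatment over all three arms, with mean NPRS from the 14-day run-in diary as prespecified covariate. Fix this before unblinding.

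Analysing simple change from run-in is not an equivalent substitute: at r = 0.5 its variance is about the same as unadjusted (simulated ratio about 1.0), and at lower correlations it is worse.

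The cost is one model term and one degree of freedom, with no new data collection. The downside is a slight loss of precision if run-in pain turns out to predict the AUC poorly.

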**Fig. 1 Fig1:**
[figure not shown]
Study design. *DN4* Diagnosing Neuropathic Pain 4 Questions, *NPRS* Numeric Pain Rating Scale

### Treatment

#### Ketamine

Ketamine will be administered in ampoules of 50 mg/5 ml intravenously with an electric syringe at the dose of 0.5 mg/kg diluted in 45 ml of physiological saline (0.9% NaCl) according to the usual procedures of the pain clinic.

#### Ketamine and magnesium sulfate

Ketamine will be given according to the protocol described above combined with an infusion of two ampoules of 0.15 g/ml of magnesium sulfate (1.5 g per 10 ml) diluted in 250 ml of physiological saline (0.9% NaCl),

#### Placebo

Physiological saline will be administered in injectable form (0.9% NaCl) in a 250-ml or 45-ml infusion via the electric syringe pump.

#### Regimen

Each patient will receive successively in random order each of the three products with a period of washout between every administration. The duration of the washout will be 5 weeks (35 days). The duration of each infusion is 2½ h per patient as follows:
*Ketamine-placebo group:* Ketamine will be administered for 2 h and placebo for 30 minutes.
*Ketamine-magnesium sulfate group:* Ketamine will be administered for 2 h and magnesium sulfate for 30 minutes.
*Placebo-placebo group:* Placebo will be administered for 2 h and placebo for 30 minutes.

The drugs used in the study (ketamine, ketamine-magnesium, and placebo) are prepared, conditioned, and released in the hospital pharmacy by one qualified person according to good manufacturing principles. Once the treatment is completed, the empty infusion bags are then returned to the packaging box, and the number of infusion bags in each dispensed container is verified and recounted at the end of the treatment by two persons totally independent of the protocol.

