### Definition of outcome measures

#### Outcome measures

The primary outcome is the AUC of pain intensity assessed on a 0–10 NPRS for a period of 5 weeks (35 days) from the day of intravenous treatment.

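### The 35-day washout coincides with the 35-day primary outcome window, and the no-carryover sample size rests on a day 28 to 60 statement that does not say whether pain is still reduced

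*Protocol article*

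**What the plan says.** All references are to the protocol article.

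- **Interval.** The abstract gives the three treatments "in random order, once at 5-week intervals". Regimen states "The duration of the washout will be 5 weeks (35 days". The opening of Methods/design assigns patients to treatment "for 1 month, in random order, with a washout period of 5 weeks between every treatment".
- **Primary outcome.** Under Outcome measures, the AUC of pain runs "for a period of 5 weeks (35 days) from the day of intravenous treatment".
- **Sample size.** Sample size calculation uses a within-patient correlation of 0.5, "owing to the crossover design and no carryover effect assumed". It then refers to an unpublished in-house study that "clearly shows that pain evaluation remains the same from 28 days to 60 days". The pain level in that interval is not given.
- **Analysis.** Statistical analysis lists treatment, sequence, subject (random) and carryover as the effects in the primary model. If the sequence-by-treatment interaction is significant, only the first period is analysed.
- **Sequences.** The treatment orders are not stated. Allocation concealment speaks of randomisation into one of three groups.

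**The concern.** The washout and the outcome window are the same days, so any effect that outlasts day 35 falls inside the next primary measurement. Whether that happens depends on how long the effect lasts. The only evidence offered is the day 28 to 60 sentence, which stands where it appears to bridge 28-day data to a 35-day endpoint. If it describes a maintained reduction, it undercuts the no-carryover assumption in the same paragraph.

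The ketamine versus placebo contrast is at stake. Depending on the sequences, placebo periods can follow an active infusion more often than ketamine periods do. Persistence would then make placebo look better and pull the unadjusted contrast towards no effect. Adjusting for carryover removes this at a cost in precision, and the stated power does not count that cost.

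**Working it through.** **1. The plan's own figures.** 35% of 164 = 57.4, which matches the stated 57. The SD of a within-patient difference is 38 × √(2 × (1 − 0.5)) = 38. The paired formula gives n = (38 × (2.393 + 1.282) / 57)² = 6.0, so 7 by the normal approximation. With the t distribution, power is 89.7% at n = 9 and 94.0% at n = 10. The stated 18 is not reproduced, but it is larger than these inputs require, and nothing below depends on how it was reached.

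**2. Timeline.** Interval 35 days − outcome window 35 days = 0 days between. If the day-28 level holds to day 60, then 60 − 35 = 25 days of the next window are covered (25/35 = 71%). Read instead as one month plus five weeks, Methods/design gives about 63 to 66 days between infusions, so day 60 would precede the next infusion. The two readings have opposite consequences, which is why they must be reconciled.

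**3. Size of carryover, as an illustration.** Assume that the average reduction, 57/28 = 2.04 points per day, persists to day 60 after either active treatment.
- Carryover: 25 × 2.04 = 51 AUC units.
- Effect over a 35-day window: 35 × 2.04 = 71.

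**4. Bias if no carryover term were fitted.** It equals carryover × (share of placebo periods that follow an active infusion − the same share for ketamine periods). P = placebo, K = ketamine, M = ketamine-magnesium.

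| Sequences | Placebo | Ketamine | Bias towards no effect |
|---|---|---|---|
| All six orders | 4/6 | 2/6 | 51 × 1/3 = 17 |
| PKM, KMP, MPK | 2/3 | 0/3 | 51 × 2/3 = 34 |
| PMK, MKP, KPM | 2/3 | 2/3 | 0 |

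17 of 71 is 24%. A least-squares fit with subject and period effects gives the same biases. With carryover terms added, the estimate returns to 71 under all three sets.

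**5. Price of the carryover term.** Within-patient variance is 38² × 0.5 = 722. At n = 18 the variance multiplier for ketamine versus placebo is 2/18 = 0.1111 without carryover terms. With period and separate carryover terms for the two active treatments (two-sided α = 1.67%, difference 57, 30 residual df, critical t 2.54):

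| Sequences | Multiplier | Variance factor | SE | 57/SE | Power |
|---|---|---|---|---|---|
| Six orders | 0.1389 | 1.25 | √(0.1389 × 722) = 10.0 | 5.7 | about 99.9% |
| Either Latin square | 0.5556 | 5.0 | √(0.5556 × 722) = 20.0 | 2.85 | about 62% |

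**6. First-period fallback.** 22/3 is about 7 patients per arm. The standardised difference is 57 / (38 × √(2/7)) = 2.81. Against a critical z of 2.39, power is 66%; against a critical t of 2.78 (12 df), it is 53%. The stated power is 90%.

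**The case against.** Three replies have force.

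First, a reader might infer that the day 28 to 60 sentence contradicts the no-carryover assumption outright. The article does not support that. It does not say whether the stable level is reduced pain or baseline pain. Baseline pain from day 28 would support the assumption, and the analysis of secondary outcomes itself speaks of the effect waning. Nor is an interval equal to the outcome window an error if the effect ends before day 35.

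Second, a reader might take the 17 or 34 units as the bias of the planned analysis. They are not. The primary model has a carryover term, and the no-carryover assumption appears only as a sample-size input. What remains is narrower. The listed effects omit period, and because first periods have no preceding treatment, a carryover term partly absorbs period differences unless period is fitted. The article may have condensed this, but it does enumerate the effects. The fallback is chosen by a pretest and is underpowered, and the stated power reflects neither analysis.

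Third, one month in Methods/design may be loose wording, since each treatment is a single infusion and the other sections agree on five weeks. The study-design figure, which is not available here, may settle it. The text alone leaves two readings.

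**Conclusion.** The point holds in a limited form. On the five-week schedule, no treatment-free time lies between one primary window and the next infusion. The no-carryover input to the sample size lacks stated support, and the evidence beside it conflicts with it on one reading only.

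The illustrated carryover of 51 units assumes that the average 28-day reduction persists unchanged to day 60 and is equal for both active treatments. The resulting loss of 0, 17 or 34 units applies only to an analysis without a carryover term and depends on sequences that the article does not give. If pain is back at baseline by day 28, carryover is zero.

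The firmer consequence concerns power. For the carryover model with period, power at n = 18 ranges from about 99.9% to about 62% according to the sequences, and for the first-period fallback it is about 53% to 66%. These figures rest on the plan's difference of 57, SD of 38 and correlation of 0.5, which are 28-day values.

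**What to change.** 1. Reconcile the abstract, Methods/design, Regimen, Outcome measures and Sample size calculation on the time between infusions. No interval is proposed here.
2. State which pain level the day 28 to 60 data show: a maintained reduction or a return to baseline.
3. Name the treatment sequences. Replace the no-carryover power statement with power for the planned carryover model, with period included, under those sequences.
4. Make the carryover-adjusted model the primary analysis, and remove the first-period analysis triggered by the interaction test.
5. Pre-specify a sensitivity check: mean diary pain over the 7 days before each infusion, reported by preceding treatment. This shows directly whether an effect is still present when the next window opens.

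The cost is a clarification of the protocol, a little more analysis of the diary data already planned, and some loss of precision. That loss is small with six orders (variance × 1.25) and substantial with a three-sequence Latin square (variance × 5.0), so the sequences should be settled before the power statement is rewritten.
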